#### Sensitivity and specificity

3.3.1

Sensitivity describes the proportion of correctly identified true cases, and thus can be calculated by dividing the number of true positive cases by the total number of positive cases in the sample (TP/TP + FN). On the other hand, Specificity describes the proportion of correctly identified negative cases, and thus can be calculated by dividing the number of true negative cases by the total number of negative cases in the sample (TN/TN + FP). ROC curves can be calculated for each substance and level of risk by plotting sensitivity on the x-axis, and (1-specificity) on the y-axis. The point at which the distance from the ROC curve (AUC) to the diagonal is maximised (Youden's *J*) can then be used to identify the most appropriate cut-off scores for each substance, at each level of risk. In effect, AUC describes the probability, if given one TP, that that TP will score higher than one TN on the test. The criterion for AUC will be set at ≥ 0.71, to indicate at least better than acceptable accuracy [42].

#### PPV and NPV

3.3.2

PPV describes the probability that an individual will be a true positive case, given a positive screen, and thus represents the proportion of true positive cases out all those receiving a positive screen (TP/TP + FP). On the other hand, NPV describes the probability that an individual will be a true negative case, given a negative screen, and thus represents the proportion of true negative cases out all those receiving a negative screen (TN/TN + FN). Table 3, Table 4, Table 5 below provide a visual reference for the diagnostic accuracy calculations using 2x2 confusion matrices.

**Table 3 tbl3:** 2x2 confusion matrix of ASSIST risk vs. diagnostic interview outcomes at the low-risk threshold for detecting any cases of problematic use with diagnostic accuracy indices.

	No disorder	Any disorder	
No use	True Negative (TN)	False Negative (FN)	NPV (TN/TN + FN)
Any disorder	False Positive (FP)	True Positive (TP)	PPV (TP/TP + FP)
	Specificity (TN/TN + FP)	Sensitivity (TP/TP + FN)

**Table 4 tbl4:** 2x2 confusion matrix of ASSIST risk vs. diagnostic interview outcomes at the moderate-risk threshold for detecting cases of moderate SUD or harmful use.

	No disorder & Mild SUD/Hazardous use	Mod. SUD/Harmful use & Severe SUD/Dependence	
Low risk	True Negative (TN)	False Negative (FN)	NPV (TN/TN + FN)
Mod. risk	False Positive (FP)	True Positive (TP)	PPV (TP/TP + FP)
	Specificity (TN/TN + FP)	Sensitivity (TP/TP + FN)

**Table 5 tbl5:** 2x2 confusion matrix of ASSIST risk vs. diagnostic interview outcomes at the high-risk threshold for detecting cases of severe SUD or dependence.

	Non-severe/Non-dependence	Severe SUD/Dependence	
Non-high risk	True Negative (TN)	False Negative (FN)	NPV (TN/TN + FN)
High risk	False Positive (FP)	True Positive (TP)	PPV (TP/TP + FP)
	Specificity (TN/TN + FP)	Sensitivity (TP/TP + FN)	

#### Likelihood ratios and clinical utility indices

3.3.3

Finally, we will also compute a range of additional metrics, including likelihood Ratios for positive (LR+) and negative (LR-) tests; Clinical Utility Index for positive (CUI+) and negative (CUI-) tests; and Cohen's weighted Kappa (interrater agreement). LR + describes the ratio of true cases to false cases, while LR-describes the likelihood of true non-cases to false non-cases. Higher ratios indicate better accuracy. CUI+ is the product of sensitivity and positive predictive value, while CUI- is the product of specificity and the negative predictive value. Finally, weighted-kappa will be used to indicate the level of agreement between risk outcomes from the ASSIST and diagnostic classifications from the clinical interview.

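### Section 3.3 misstates the likelihood ratios, transposes the ROC axes and mislabels ASSIST rows in Tables 3 and 4; wording and labels need correcting before analysis

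*Protocol article*

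**What the plan says.** The points are all in section 3.3 of the protocol article. Section 3 names diagnostic accuracy among the primary outcomes.

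- **Likelihood ratios (section 3.3.3).** "LR + describes the ratio of true cases to false cases, while LR-describes the likelihood of true non-cases to false non-cases". The LR- clause runs straight into one direction rule for both ratios: "LR-describes the likelihood of true non-cases to false non-cases. Higher ratios indicate better accuracy".
- **ROC curve (section 3.3.1).** Curves are drawn by "plotting sensitivity on the x-axis, and (1-specificity) on the y-axis". The same section states that "The criterion for AUC will be set at ≥ 0.71" and that "AUC describes the probability, if given one TP, that that TP will score higher than one TN on the test".
- **Table 4 (section 3.3.2).** The table is captioned as applying "at the moderate-risk threshold for detecting cases of moderate SUD or harmful use". Its columns set no or mild disorder (hazardous use) against moderate and severe disorder (harmful use and dependence). Its two ASSIST rows are *Low risk* and *Mod. risk*. The opening text of section 3.3 sets the moderate threshold as none or mild against moderate or severe.
- **Table 3 (section 3.3.2).** The columns are *No disorder* and *Any disorder*. The ASSIST rows are *No use* and *Any disorder*.
- **Table 5, for contrast.** Its test-negative row is explicitly pooled as *Non-high risk*.

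**The concern.** An analyst or reader who takes these statements at face value would go wrong in four places.

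1. TP/FP and TN/FN are predictive odds. They depend on how many cases and non-cases were recruited, whereas likelihood ratios depend only on sensitivity and specificity. Recruitment here is stratified by risk level, so the case mix is partly set by design, and odds of this kind would not carry over to another setting.
2. If standard software reports the conventional LR-, a reader using the protocol's single direction rule would read it backwards, because for that index lower is better.
3. The axes as written give a curve whose area is the complement of the AUC, which conflicts with the acceptance criterion in the same section.
4. Table 4 has no cell for high-risk ASSIST respondents, a planned third of the minimum sample per substance (40 of 120, section 2.2.2). Table 3 has an ASSIST row named after an interview outcome, so which app result counts as positive there is not defined.

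**Working it through.** No stated sample size, power or alpha depends on these definitions, so there is no figure of the plan to reproduce. Each statement is compared with the standard definition.

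**1. Likelihood ratios.** Inputs: sensitivity 0.70 (used in section 3.5); specificity 0.80 (assumption). The case mixes are 40:40, the 1:1 ratio that section 3.5 aims for where possible, and 40:80 and 80:40. The last two are what 40 low, 40 moderate and 40 high would give at the high and moderate thresholds if diagnosis tracked risk level.

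Standard: LR+ = sens/(1 - spec) = 0.70/0.20 = 3.50. LR- = (1 - sens)/spec = 0.30/0.80 = 0.375.

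As described, with N+ cases and N- non-cases:
- TP/FP = LR+ × (N+/N-)
- TN/FN = (1/LR-) × (N-/N+)

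| Cases:non-cases | TP/FP | TN/FN |
|---|---|---|
| 40:40 | 28/8 = 3.50 | 32/12 = 2.67 |
| 40:80 | 28/16 = 1.75 | 64/12 = 5.33 |
| 80:40 | 56/8 = 7.00 | 32/24 = 1.33 |

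TP/FP equals LR+ only at 1:1. TN/FN is a different index from LR-; at 1:1 it is the reciprocal (1/0.375 = 2.67).

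Direction: take a test with sens = spec = 0.80 and an uninformative one with sens = spec = 0.50, both at 1:1. TN/FN is 0.80/0.20 = 4.0 against 0.50/0.50 = 1.0, so higher is better for the quantity described. The conventional LR- is 0.20/0.80 = 0.25 against 0.50/0.50 = 1.0, so lower is better for the index named.

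**2. ROC axes.** Exchanging the axes reflects the curve in the diagonal, so the area becomes 1 - AUC:
- 0.71 becomes 0.29
- 0.80 becomes 0.20
- 0.90 becomes 0.10

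An instrument exactly at the criterion would show 0.29. The distance from the curve to the diagonal is the same after reflection, so the cut-off chosen by maximising that distance does not move. A numerical check with binormal curves gave the same cut-off both ways.

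**3. Table 4.** Inputs: 40 respondents per ASSIST level (section 2.2.2); assumed shares with moderate or severe disorder of 10%, 50% and 90% in the low, moderate and high levels. Cases are then 4, 20 and 36, and non-cases 36, 20 and 4.

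- High-risk counted as positive: TP = 20 + 36 = 56, FN = 4, FP = 20 + 4 = 24. Sensitivity = 56/60 = 0.93; PPV = 56/80 = 0.70.
- Rows as labelled, high-risk omitted: TP = 20, FN = 4, FP = 20. Sensitivity = 20/24 = 0.83; PPV = 20/40 = 0.50.

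A second assumed cross-table, also with 40 per level, moved the same way: sensitivity from 60/64 = 0.94 to 22/26 = 0.85, and PPV from 60/80 = 0.75 to 22/40 = 0.55.

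**4. Table 3.** Section 2.2.2 says the app returns low, moderate or high risk. Section 3.3 says positivity comes from the ASSIST risk category and that cut-offs are re-derived by ROC analysis. *Any disorder* is an interview category, and *No use* is not one of the three app results. Neither label states an ASSIST result at a derived cut-off.

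**The case against.** Much can be said for the plan.

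- **Likelihood ratios.** A reader might infer that the protocol's own reading of LR- is reversed. It is not: at a fixed case mix TN/FN rises as the test improves, so the direction rule fits the quantity described and fails only for the conventional index. The wording could also mean rates rather than counts. LR+ would then be right, but LR- would be spec/(1 - sens), still the reciprocal of the usual index. The ratios are listed as additional metrics with no acceptance criterion, and at the 1:1 ratio that section 3.5 hopes for, TP/FP equals LR+.
- **ROC.** A reader might infer that a good instrument would be failed against 0.71. The criterion and the verbal description of AUC both follow the standard orientation, and standard software would too. Only the axis labels are out of line. The description's use of TP and TN for case and non-case is loose wording, not a separate error.
- **Table 4.** A reader might infer that high-risk respondents are to be excluded. The text of section 3.3 defines a threshold that splits the whole sample, section 3.3.2 offers the tables as a visual reference, and Table 2 marks exclusions explicitly where they are meant. The row label is a slip, not a rule.
- **Weighted kappa.** A reader might infer that kappa cannot be computed with three ASSIST levels and four diagnostic levels. The article does not state the mapping, but the analysis plan it cites may do so, and the *No use* row hints at a fourth level. This is not a finding.

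What stands is that the LR wording, the axis order and the row labels are wrong as printed. The pooled wording in Table 4's columns and in Table 5 also shows that pooling is written out elsewhere in the same set of tables.

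**Conclusion.** The concern holds as a set of misstatements of moderate severity. Section 3.3.3 does not describe the conventional likelihood ratios. Section 3.3.1 contradicts itself on the ROC axes. Table 4 leaves high-risk respondents without a cell, against the section's own threshold. Table 3 names an ASSIST row by an interview outcome.

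The dependence of TP/FP and TN/FN on case mix, and the change from AUC to 1 - AUC, are algebraic and need no assumption. The sizes for the likelihood ratios rest on an assumed specificity of 0.80. The Table 4 figures rest on assumed case rates and apply only if the row label were followed literally. No sample size, power figure or Youden cut-off changes.

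The documents do not show that the planned results will be wrong, only that the printed definitions would make them so if followed.

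**What to change.** - **Section 3.3.3:** state LR+ = sens/(1 - spec), higher is better, and LR- = (1 - sens)/spec, lower is better, in place of the single direction sentence.
- **Section 3.3.1:** put 1 - specificity on the x-axis and sensitivity on the y-axis.
- **Table 4:** label the test-positive row *Moderate or high risk*.
- **Table 3:** label both rows by the ASSIST result, below against at or above the derived low-risk cut-off.

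The cost is wording and table labels only, with no change to recruitment, data collection, sample size or power. The same definitions should be checked in the supplementary analysis plan so that the two documents agree before analysis.

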### Cultural acceptability

3.4

The final section of the app includes questions to assess cultural acceptability. Participants are asked to rate their agreement to three questions on a 5-point Likert scale, using facial expression emojis, ranging from 0 (frown) to 5 (smile). The three questions are: “How easy was it to use this iPad to answer our questions?“, “Was it okay for us to ask these questions?“, and “Were the questions easy to understand?” Responses will be quantified and used to assess acceptability, together with the time taken to complete the app. In addition, research assistants will be on-hand to ask participants about their qualitative experiences using the app in a semi-structured yarning style discussion.

### Sample Size and Power Calculations

**3.5**

For the validity assessments, a series of power calculations were conducted to determine the minimum sample size needed to detect a large between-groups effect, with type-I, and type-II error rates of 5 % (corresponding to α = 0.05), and 10 % (corresponding to an *a priori* power of 90 %) respectively. Where possible, we will also aim to recruit a 1:1 ratio of participants for each group (i.e., positive/negative cases), and so a 1:1 ratio of participants was used here. Using these parameters as default, we conducted the following power calculations in G-power [43].

For each regression model assessing concurrent validity, it was determined that a minimum of 111 participants are needed for each model (corresponding to line-of-best-fit slope of 0.3). For each logistic regression model assessing concurrent validity with the independent assessment, a total sample size of 62 using each substance was determined. The additional parameters used in this analysis included a probability of reaching diagnosis in the diagnosis present group of 0.70 (corresponding to a sensitivity of 70 % and an Odds Ratio of 2.33 [0.70/0.30]), versus a chance probability (i.e., 50%) in the diagnosis absent group. These parameters yielded a total sample size of 62 individuals (approximately 31 in each group diagnosis present/absent assuming 1:1 sampling). For each ANOVA model assessing discriminant validity, a minimum of 96 participants using each substance are required to power the analysis (corresponding to *η*^2^ = 0.14 [44]). Based on this, the minimum number of participants to detect a large effect (Cohens’ *d* > 0.80 [45]) was 38 participants for each group. This corresponds to thirty-eight low risk, thirty-eight moderate risk, and thirty-eight high-risk individuals for each substance (which equals approximately 114 participants for each given substance). For the reliability assessment, we also calculated the minimum sample size required to detect reliability coefficients >0.70, setting the type-I error rate to 0.05, with a minimum power of 0.90, with the number of scale items equal to 4 (tobacco) or 5 (all other substances). This method has been suggested previously [46] and has been used widely in health and medical research settings [47]. The result was a minimum sample size of 38 for a 5-item scale, and 40 for the 4-item scale. We elected to use 40 as the minimum sample size required for consistency.

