#### Independent clinical evaluation

2.3.4

Participants recruited from the DASSA withdrawal service will also undergo an independent clinical evaluation from an addiction medicine specialist, trained to diagnose the presence or absence of ICD-11 and DSM-5-TR disorders related to substance use. The registrar will be blinded from the outcome of the earlier assessment and will provide a clinical opinion as to whether the individual in their care meets the diagnostic threshold for hazardous use, harmful use or dependence (ICD-11) and substance use disorder (DSM-5-TR) for each of the five substances. In all cases, the individual will be known to the clinician (as a patient of the service).

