#### Concurrent validity

3.2.1

Concurrent validity will be assessed in two ways. First, a confirmatory approach will assess the partial-order (Spearman's Rho [ρ]) correlation between ASSIST SSI scores for each scale, and the total number of DSM-5-TR and ICD-11 diagnostic symptoms reported for that substance. The use of partial correlations will help to control for the effects of other substances and demographic factors. Benjamini-Hochberg (BH) correction will be used for each correlation to control the False Discovery Rate (FDR) [41]. BH-corrected significant (FDR <0.05) partial correlation ρ ≥ 0.5 will indicate concurrent validity.

The second (exploratory) approach will involve assessing the relationship between ASSIST SSI scores and the number of DSM-5-TR/ICD-11 symptoms through linear and quadratic regression models. For every substance, a regression plot will map the number of ICD-11/DSM-5-TR symptoms reported (vertically along the y-axis) as a function of the ASSIST SSI score (horizontally on the x-axis). As there are five substances, and two distinct classification systems, a total of 20 separate regression models will be carried out (10 linear, and 10 quadratic). For each substance, a significant linear and/or quadratic relationship (*p* < 0.05) is expected to be found between the number of symptoms reported and the average ASSIST scores. Model fit indices will be reported, and models will be compared using AIC and BIC values, to prevent overfitting. Models with the lowest AIC/BIC values will be selected.

A final check for concurrent validity (depending on sufficient data) will investigate the relationship between ASSIST SSI scores for each substance, and the outcomes from the independent clinical assessment by an Addiction Medicine Specialist. For each substance, a logistic regression model will be used to assess the probability of reaching a diagnosis, per unit score increase on the ASSIST. For each substance, a significant model (*p* < 0.05) is expected to be found between the ASSIST scores and the diagnosis probability.

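### The sample size of 62 for the logistic check against the independent clinical assessment does not follow from its stated inputs: 0.70 versus 0.50 at 90% power needs about 248

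*Protocol article*

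**What the plan says.** Section 3.5 sets defaults for all its validity calculations: "type-I, and type-II error rates of 5 % (corresponding to α = 0.05), and 10"%, that is 90% power, with a 1:1 ratio of positive to negative cases where possible.

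For the logistic models against the independent assessment it adds "a probability of reaching diagnosis in the diagnosis present group of 0.70 (corresponding to a sensitivity of 70 % and an Odds Ratio of 2.33", which it writes as 0.70/0.30, "versus a chance probability (i.e., 50%) in the diagnosis absent group". The result: "These parameters yielded a total sample size of 62 individuals (approximately 31 in each group diagnosis present/absent assuming 1:1 sampling". The 62 applies to each substance. Sidedness is not stated.

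Section 3.2.1 (Concurrent validity) describes the analysis itself: "a logistic regression model will be used to assess the probability of reaching a diagnosis, per unit score increase on the ASSIST". It calls this a final check, to be run if there are enough data, and expects p < 0.05 for each substance.

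Section 2.3.4 says who contributes: "Participants recruited from the DASSA withdrawal service will also undergo an independent clinical evaluation". Section 2.2.4 describes these participants as a higher-risk group.

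**The concern.** There are three separate problems.

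1. **Inputs and output disagree.** Section 3.5 gives everything a two-proportion sample size needs except sidedness. A difference of 0.70 versus 0.50 is modest, and 31 per group is far too few to detect it with 90% power.
2. **The calculation is not for the planned model.** Section 3.5 describes two groups. Section 3.2.1 plans a regression on a numerical score. A calculation for that regression needs an effect tied to the spread of the score, and none is given.
3. **The 1:1 split has no source.** Only withdrawal-service participants are assessed, and nothing in the plan samples them on diagnosis.

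What is at stake is a published power statement that its own inputs contradict. It is also the only number in the article that indicates how much data this check needs.

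**Working it through.** **Inputs (section 3.5).** p₁ = 0.70, p₂ = 0.50, 1:1, alpha 0.05, power 90%. z = 1.960 two-sided or 1.645 one-sided; z for power = 1.2816.

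**Odds ratio.** (0.70/0.30)/(0.50/0.50) = 2.33. This reproduces.

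**The plan's 62, by the calculation described.** With p̄ = 0.60,

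n per group = [z_α √(2p̄(1−p̄)) + z_β √(p₁(1−p₁) + p₂(1−p₂))]² / (p₁−p₂)²

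- √0.48 = 0.6928 and √(0.21 + 0.25) = 0.6782.
- Two-sided: (1.3579 + 0.8692)² / 0.04 = 124.0, so 124 per group and 248 in total.
- One-sided: (1.1396 + 0.8692)² / 0.04 = 100.9, so 101 per group.

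The figure 62 does not reproduce. A continuity correction raises the two-sided figure to 134 per group. Logistic Wald formulas with a balanced binary predictor give 249 to 257 in total.

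**Power at 31 + 31.** Φ[(0.20√31 − z_α × 0.6928)/0.6782]

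- Two-sided: Φ[(1.1136 − 1.3579)/0.6782] = Φ(−0.360) = 35.9%. Exact power is 37.2% for the chi-square test and 27.8% for Fisher's test.
- One-sided: Φ[(1.1136 − 1.1396)/0.6782] = Φ(−0.038) = 48.5%.
- Two-sided, with the 62 split 80:20 or 90:10: 27% or 19%.

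**Calculations that do give a figure at or near 62 (two-sided, 90% power).**

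| Calculation | Result | Is it what section 3.5 describes? |
|---|---|---|
| Two groups, 0.70 vs 0.30 | (1.3859 + 0.8305)² / 0.16 = 30.7, so 31 per group | No: the odds ratio would be (0.70/0.30)² = 5.44 |
| One sample, 0.70 vs 0.50 | (1.960×0.5 + 1.2816×0.4583)² / 0.04 = 61.4, so 62 in total | No: there is no second group |
| Normal score, odds ratio 2.33 per SD, half diagnosed | 59, 70, 73 or 90 in total, by formula | No: no per-SD effect is stated, and there are no two groups of 31 |

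In the last row, 59 is the Hsieh formula: (1.960 + 1.2816)² / (0.25 × 0.8473²) = 58.5, where 0.8473 = ln 2.33. The variance-corrected Wald formula gives 70, the likelihood-ratio formula 73 and the uncorrected Wald formula 90.

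**Power of 62 for a regression on the score.** These figures assume an odds ratio of 2.33 per SD of a normally distributed score and a two-sided test. Neither assumption is in the protocol.

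| Assumed proportion diagnosed | Power at n = 62 |
|---|---|
| 50% | Simulation: about 84% (Wald) to 86% (likelihood ratio). Formulas: 77%, 85%, 87%, 92% |
| 80% | Simulation: 71–75%. Hsieh: 76% |
| 90% | Simulation: 49–55%. Hsieh: 52% |

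In the simulations the proportion is the probability of diagnosis at the mean score. The 80% and 90% rows are illustrations.

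**The case against.** The strongest reply is that section 3.5 offers 62 for a logistic regression, and section 3.2.1 plans that regression on the score, so a two-proportion calculation tests the wrong thing. This stands in part. A reader might infer that the planned check has only 36% power, and the documents do not support that. The 36% belongs to the two-group design as worded. For the regression, under the per-SD assumption above and an even split, 62 falls only somewhat short of 90%. But the objection does not rescue the text, which derives 62 from 0.70, 0.50 and two groups of 31.

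A reader might also infer that 62 must have come from the per-SD model. Two other calculations come closer, and the documents do not say which was run.

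Third, it is tempting to say that the sample will not be 1:1. The documents give no diagnosis rates, and section 3.5 presents 1:1 as an aim and an assumption. In a withdrawal service most participants may be diagnosed for a main substance and few for an uncommon one, so imbalance could run either way. What stands is that the design provides nothing to produce an even split for each of five substances.

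Finally, the consequences are limited. Section 3.2.1 makes this a final check subject to sufficient data. It sets no rule that a non-significant model counts against validity. The recruitment target of 40 per risk level in section 2.2.2 is not built on 62.

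**Conclusion.** The concern holds for the sample size and power as written. The stated inputs require about 248 in total, four times 62. The stated 62 has about 36% power two-sided, or 48% one-sided, against a claimed 90%. Leaving sidedness open does not close the gap. These results rest only on section 3.5's own inputs and the standard two-proportion formula, and exact calculations agree.

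It also holds that sections 3.5 and 3.2.1 describe different analyses and that the 1:1 assumption is unsupported. It does not follow that the planned regression is badly underpowered. That depends on the effect per SD of score and the proportion diagnosed, and the article gives neither. This should be fixed, but it is not critical, because the study's main conclusions do not rest on this check.

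**What to change.** - In section 3.5, withdraw the statement that 62 gives 90% power for 0.70 versus 0.50.
- Restate the power for the regression that section 3.2.1 plans, naming the test used in the software, its sidedness, the effect scale (per point or per SD of score) and the assumed proportion diagnosed.
- Correct or remove the description of 31 per group so that it matches.
- Say that the proportion diagnosed in the withdrawal service is unknown for each substance, and show power over a range.

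If the sponsor adopts the per-SD model, wording such as this would be accurate: *With 62 participants, a two-sided 5% test and an assumed odds ratio of 2.33 per SD of a normally distributed score, power is about 84–86% by simulation (77–92% by formula) if half are diagnosed. It is about 71–76% if 80% are diagnosed and about 49–55% if 90% are.* If another model was intended, its own figures should replace these.

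The cost is wording only, with no added recruitment. The stated power becomes less favourable.

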#### Recruitment

2.2.2

A stratified sampling strategy will be employed to target individuals across the spectrum of risk for each of the five substances included in the Pitjantjatjara ASSIST (“*the app*”, i.e., alcohol, tobacco, cannabis, methamphetamine and inhalants). Since *the app* focuses on these five substances only, and uses existing WHO-ASSIST 3.1 cut-off scores to determine three corresponding levels of risk for each (i.e., low, moderate or high), there are a total of 15 (5x3) possible substance/risk combinations. We will aim to recruit a minimum of 40 individuals to satisfy each of those outcomes (e.g., 40 participants each for low, moderate and high-risk, for each of the substances This could require up to 600 participants, though the total will likely be lower since many use multiple substances. Recruitment will occur until we meet the minimum number for each group, or until the investigators deem it unnecessary to continue. Further details related to the power calculations is found in section 3.5. *Sample Size and Power Calculations* below.

To capture a broad range of participants, we will recruit from a variety of health and welfare settings. The goal is to recruit individuals who are likely to be engaged in low and/or moderate risk alcohol, tobacco or other drug use (e.g., from general health and welfare settings), and those who are more likely to be engaged in use which places them at higher-risk of dependence (e.g., from withdrawal services or other inpatient/outpatient treatment settings). Recruitment will occur at seven different sites across South Australia, by word-of-mouth at each service or setting, where Aboriginal health workers will approach potential participants directly.

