#### Discriminant validity

3.2.2

Discriminant validity assesses the extent to which an instrument can differentiate between two (or more) theoretically independent groups. In this study, groupings will be determined by ICD-11 and DSM-5-TR diagnostic categories respectively. Differences between scores as a function of diagnostic classification will be assessed using initial one-way ANOVA, with a series of planned pairwise t-tests to confirm group-level differences. Ten separate ANOVA models will assess whether differences exist in the distribution of ASSIST scores between groups for each substance and classification system (i.e., 5-substances x 2-systems). Table 1 below outlines the planned analysis for the two tests.

**Table 1 tbl1:** One-way ANOVA models assessing group differences for ICD-11 (Model set 1) and DSM-5-TR (Model set 2).

Model set	Diagnostic Severity Group (per substance)			
1	No disorder	Hazardous use	Harmful use	Dependence
2	No SUD	Mild SUD	Moderate SUD	Severe SUD

In the first set of models, score distributions will be compared based on ICD-11 diagnostic classifications for each substance, while the second set of models will compare score distributions based on DSM-5-TR diagnostic classifications. If a significant omnibus test is found (i.e., *p* < 0.05) for each substance/classification, as expected, three planned (*a priori*) pairwise comparisons using BH-correction (setting FDR <0.05) will assess the magnitude and direction of those score differences.

Table 2 below outlines the planned comparisons to be carried out. For each substance, the first set of planned comparisons will assess the ability of the Pitjantjatjara ASSIST SSI to discriminate between the absence of DSM-5-TR or ICD-11 disorder, versus mild SUD and hazardous use, respectively. The second set of comparisons will assess the ability of the SSI to discriminate between mild vs moderate SUD; or between hazardous vs harmful use, respectively. The third set of comparisons will assess the ability of the SSI to assess risk between moderate vs severe SUD; and between harmful use vs dependence, respectively (see Table 2).

**Table 2 tbl2:** Planned (A vs. B) pairwise comparisons of ASSIST scores by ICD-11/DSM-5-TR diagnoses.

Planned comparisons		No disorder/No SUD	Hazardous use/Mild SUD	Harmful use/Moderate SUD	Dependence/Severe SUD
1	Low risk	A	B	*excluded*	*excluded*
2	Mod. risk	*excluded*	A	B	*excluded*
3	High risk	*excluded*	*excluded*	A	B

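### The 38 per compared group is multiplied by three ASSIST risk tiers, but the pairwise tests compare four interview-diagnosis groups, so 114 to 120 per substance does not secure 38 per group

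*Protocol article*

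**What the plan says.** **Sample size.** Section 3.5 sets the general parameters ("with type-I, and type-II error rates of 5" and 10 per cent, so 90% power). Equal groups are assumed: "so a 1:1 ratio of participants was used here". For the ANOVA, "a minimum of 96 participants using each substance are required to power the analysis", at η² = 0.14. For a large pairwise effect (Cohen's d of 0.80) the minimum "was 38 participants for each group". The next sentence turns this into a total: "This corresponds to thirty-eight low risk, thirty-eight moderate risk, and thirty-eight high-risk individuals for each substance", given as about 114 per substance.

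**Analysis.** In section 3.2.2 the groups are not risk tiers: "groupings will be determined by ICD-11 and DSM-5-TR diagnostic categories respectively". Table 1 lists four per substance: no disorder, hazardous use or mild SUD, harmful use or moderate SUD, and dependence or severe SUD. Table 2 plans three adjacent-pair comparisons, BH-corrected at FDR 0.05. The first sets no disorder against hazardous use or mild SUD.

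**Recruitment.** Section 2.2.2 sets minimum quotas by tier, "40 participants each for low, moderate and high-risk, for each of the substances", with tiers defined by the existing WHO-ASSIST 3.1 cut-offs on the app score. Recruitment runs until these are met or the investigators judge it unnecessary to continue.

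**The concern.** The per-group size belongs to one grouping and the total to another. The 38 is a requirement for each group in a two-group comparison. Those groups are fixed by the interview and there are four of them, whereas the multiplication uses three groups fixed by the app.

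The quotas inherit the mismatch. Section 3.3 aligns the low-risk tier with hazardous use or mild SUD, the moderate tier with harmful use or moderate SUD, and the high tier with dependence or severe SUD. No tier stands for no disorder, so one arm of the first planned comparison has no quota. The other three groups have one only so far as app tier and diagnosis agree, and that agreement is what the study sets out to measure.

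Validity is among the primary outcomes, and the adjacent-pair tests are the planned evidence that the score separates neighbouring levels of severity. A pair that fails to separate because one group is small could be read as poor discrimination by the app.

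**Working it through.** **Inputs.** From section 3.5: alpha 0.05 (sidedness not stated), power 90%, equal groups, d = 0.80, η² = 0.14, 96 for the ANOVA, 38 per group, 114 per substance. From section 2.2.2: 40 per tier, so 3 × 40 = 120 per substance. From section 3.2.2: four groups and three BH-corrected pairs.

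**1. The ANOVA figure.** f = √(0.14/0.86) = 0.4035, conventionally rounded to 0.40. Power comes from the noncentral F distribution with noncentrality f²N and degrees of freedom k − 1 and N − k. Smallest N in equal groups for 90% power at alpha 0.05:

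| f | k = 3 | k = 4 |
|---|---|---|
| 0.40 | 84 | **96** |
| 0.4035 | 81 | 92 |

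The stated 96 reproduces with f = 0.40 and four groups (24 each, power 91%). It does not reproduce with three.

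**2. The 38 per group.** Power comes from the noncentral t distribution with noncentrality d√(n/2) and 2n − 2 degrees of freedom.

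- Two-sided 0.05: n = 34 per group.
- Two-sided 0.033 (the mean of the three BH thresholds 0.0167, 0.033 and 0.05): n = 38, power 90.4%.
- One-sided 0.05/3: n = 38, power 90.4%.

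So 38 is reachable under an alpha adjusted for three tests. The article does not say which setting was used, so both adjusted settings are assumptions.

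**3. The total.** 3 × 38 = 114 is correct arithmetic for three groups. For the four groups of Table 1, 4 × 38 = 152 (or 4 × 40 = 160). Split evenly, the stated totals give 114/4 = 28.5 and 120/4 = 30 per group.

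**4. Pairwise power at d = 0.80, equal groups.**

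| n per group | two-sided 0.05 | two-sided 0.033 (same as one-sided 0.05/3) | two-sided 0.0167 (strictest BH step) |
|---|---|---|---|
| 28.5 | 84.3% | 79.7% | 70.8% |
| 30 | 86.1% | 81.8% | 73.5% |
| 34 | 90.2% | 86.7% | 79.7% |
| 38 | 93.1% | 90.4% | 84.7% |

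**5. Unequal groups**, two-sided 0.05, with noncentrality d√(n₁n₂/(n₁ + n₂)). These splits are illustrations and are not taken from the article.

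- 20 vs 20: 69%. This would be the first comparison if 40 low-tier participants divided evenly between no disorder and hazardous use or mild SUD.
- 15 vs 40: 74%.
- 10 vs 40: 60%.
- 30 vs 60: 94%.

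**6. The omnibus test.** With k = 4, equal groups and f = 0.4035, power is 95.8% at N = 114 and 96.7% at N = 120.

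**The case against.** The strongest reply is that the plan never says 120 people per substance will be divided over four groups. The quotas are minima, the overall total may reach 600, and section 2.2 recruits abstainers as well as users. On the alignment in section 3.3, three tiers may be meant to fill the three disorder groups, while people recruited for other substances supply the no-disorder group. If that group became large, the first comparison would gain power (30 vs 60 gives 94% at two-sided 0.05). Tier is also a reasonable proxy for diagnosis, and recruiting from both general and withdrawal settings should spread severity.

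Much of this stands. It rules out saying that the design will fall short of 38 per group, or that tier quotas tell us nothing about diagnosis groups. It does not supply a minimum for any diagnosis group, and a large no-disorder group does nothing for the second and third comparisons. Section 3.5 also words its ANOVA requirement in terms of people using each substance, which sits awkwardly with counting non-users.

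Three stronger readings are tempting and are not supported:

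- **That 38 is a miscalculation, because two-sided 0.05 gives 34.** The article states no sidedness, and three corrected tests are planned. Two plausible adjusted settings give 38 exactly.
- **That 34 per group, 136 in total, would suffice.** It reaches 90% only without the planned correction: about 87% at 0.033 and 80% at 0.0167.
- **That discriminant validity as a whole is underpowered.** The omnibus ANOVA is not, under equal groups at η² = 0.14.

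The 71 to 73% figure should also be read with care. BH applies 0.05/3 only to the smallest p-value, and the other thresholds are 0.033 and 0.05.

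**Conclusion.** The point holds as a mismatch of group definitions. Section 3.5 sizes the pairwise tests for three app tiers, section 3.2.2 runs them on four interview-diagnosis groups, and the ANOVA size in section 3.5 already fits four. The stated 114 to 120 per substance therefore does not secure 38 per compared group. It may still be reached if enough abstainers and users of other substances are enrolled and if tier tracks diagnosis closely.

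Under an even split over four groups, power for d = 0.80 is 84 to 86% uncorrected, about 80 to 82% at an alpha that reproduces 38, and 71 to 73% at the strictest BH step, against the stated 90%. Only the three adjacent-pair tests are affected. The result rests on the even split, which is assumed, and on d = 0.80, which is the plan's own. Uneven groups could make individual pairs better or worse.

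**What to change.** **Section 3.5.** Restate the pairwise calculation for four diagnosis groups. State the alpha, sidedness and any multiplicity adjustment behind 38. Then do one of the following:

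- give the pairwise power expected at 114 to 120 per substance after BH correction, with a short table for unequal groups; or
- state 152 per substance as the size that matches 38 per group, noting that it does so only if the groups fill evenly.

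Do not replace 38 with 34 per group, which leaves out the BH correction.

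**Section 2.2.2.** Keep the tier quotas and add a running tally of interview-diagnosis groups for each substance. Name the classification system that governs the tally, since ICD-11 and DSM-5-TR groups need not coincide. Under one system this is 5 × 4 = 20 cells beside the existing 15; both systems would need 40.

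**Cost.** The interview diagnoses are already collected, so the cost is some extra tracking and a less favourable stated power. Restating the power needs no added participants. Adopting 152 could need more, by an amount that depends on how many people count towards several substances. The tally is useful only while recruitment is open, because group sizes cannot be corrected afterwards.
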